## Abstract

**Background:**

A Cochrane review of mistletoe therapy concludes that there is some evidence that mistletoe extracts may offer benefits on measures of quality of life during chemotherapy for breast cancer, but these results need replication. Our aim is to add to this evidence base by initially testing the feasibility of a UK pilot placebo-controlled, double-blind randomised controlled trial of mistletoe therapy in patients with breast cancer undergoing chemotherapy with or without radiotherapy.

**Methods/design:**

A mixed phase pilot placebo-controlled, double-blind randomised controlled trial of mistletoe therapy in patients with breast cancer (EudraCT number: 2018-000279-34). There will be three arms (groups) in the trial: Iscador M, Iscador P, with physiological saline as the placebo. The aim is to recruit 45 adult patients with a new diagnosis of early or locally advanced breast cancer, up to 12 weeks following definitive breast surgery whose standard treatment plan includes chemotherapy with or without radiotherapy. They will be taught to administer the mistletoe and breast cancer (MAB) therapies subcutaneously. MAB therapy will continue throughout their standard chemotherapy and radiotherapy and 1 month beyond. The main outcome of the MAB study is the feasibility of conducting such a trial within the NHS in order to inform a future fully powered investigative trial. Feasibility will be measured through recruitment, retention and patient experience using clinical research forms, patient diaries, cancer-related questionnaires and qualitative interviews conducted with both patients and oncology staff.

**Discussion:**

This trial is the first of its kind in the UK. Currently, mistletoe therapy is mostly available through private practice in the UK. Completion of this feasibility study will support applications for further funding for a fully powered randomised controlled trial which will measure effectiveness and cost-effectiveness of this herbal therapy.

## Background

In Europe, *Viscum album* L. (mistletoe) is the most commonly used therapy by patients with cancer and is integrated into conventional oncology treatment programmes in Germany, Switzerland and Holland. Despite this use of mistletoe therapy, it is only relatively recently that it has been the subject of randomised controlled trials (RCTs), although few are placebo-controlled trials. A Cochrane review conducted in 2008 concluded that the effects of mistletoe on the adverse effects of chemotherapy and radiotherapy were a reduction of these effects and/or improvement of quality of life (QOL) in breast cancer patients, but that the magnitude of these effects could not be reliably estimated from current trials and was not pooled in a meta-analysis [1]. A 2019 systematic review included 28 publications of mistletoe therapy for cancer which included 17 RCTs that report quality-of-life outcomes [2]. The authors conclude ‘to date, no clear statement regarding the efficacy of mistletoe treatment can be derived from randomised controlled studies’. A 2020 systematic review of mistletoe therapy for cancer patients included 26 publications with 30 data sets from RCTs and controlled trials in a meta-analysis [3]. They acknowledge the heterogeneity of the data and report a pooled standardised mean difference for global quality of life (all cancers) after treatment with mistletoe extracts vs. control (*d* = 0.61 (95% *CI* 0.41–0.8181, *p* < 0.00001)). Both reviews acknowledge the limitations of the data and the uncertainties surrounding the lack of placebo-controlled trials in mistletoe therapy. This uncertainty is coupled with the fact that potential recruitment of cancer patients into placebo controlled RCTs of mistletoe on mainland Europe is limited by the popularity of the therapy. This is not the case in the UK, where trial participants are likely to be naïve to mistletoe as a therapeutic agent. Whilst mistletoe can be prescribed in the UK, this is mostly through private practice, despite its potential to improve the patient experience of cancer care, a major priority of the NHS cancer plan [4]. The primary aim of this external mixed phase pilot trial, the first of its kind in the UK, is to test the feasibility of a placebo-controlled, double-blind RCT of mistletoe therapy in patients with breast cancer undergoing chemotherapy with or without radiotherapy in the NHS setting.

## Methods

### Design

The design is a pilot mixed phase, placebo controlled, double blind external RCT of mistletoe therapy in patients with breast cancer undergoing chemotherapy with or without radiotherapy. The primary aim of feasibility of the trial will be considered in terms of recruitment, retention, attrition, blinding and acceptability to patients and health professionals. There will be three arms (groups) in the trial: Iscador M, Iscador P (mistletoe therapy) with physiological saline as the placebo.

This mixed phase pilot study is an initial step to explore the innovative provision of mistletoe therapy within conventional NHS cancer care. Our primary aim is to inform feasibility and identify modifications needed in the design of a larger trial, ensuring hypothesis testing.

### Participants

We aim to recruit 45 adult patients with a new diagnosis of early or locally advanced breast cancer, up to 12 weeks following definitive breast surgery whose standard treatment plan includes chemotherapy with or without radiotherapy. The patients in this feasibility trial will be recruited via one site the Bristol Haematology and Oncology Centre (BHOC) at University Hospitals Bristol NHS Foundation Trust. 

### Inclusion and exclusion criteria

Potential participants will include adults 18 years or over with histologically verified early or locally advanced invasive breast cancer and with planned adjuvant chemotherapy, with or without radiotherapy and able to be randomised within 12 weeks of surgery. Patients who are to receive only radiotherapy will be excluded as this treatment is generally well tolerated and of short duration. They must be willing to self-administer or have a nominated person administer injections. Their Eastern Cooperative Oncology Group (ECOG) performance status must be 0 or 1, and they should have no active, uncontrolled infection. Female participants of childbearing age must be willing to adopt adequate contraceptive measures, and males must follow the chemotherapy guidance of the BHOC with regard to contraception. Patients will be excluded if they are receiving immunomodulatory therapy, receiving endocrine therapy as a stand-alone treatment, have previously had invasive breast cancer or bilateral breast cancer or have chronic viral infections such as hepatitis B and C and HIV known allergy to mistletoe, or be using/have had mistletoe within the last 5 years, acute inflammatory or pyrexial conditions, chronic granulomatous disease, active auto-immune diseases, or hyperthyroidism with tachycardia. Where appropriate, patients who are recommended to receive trastuzumab and/or endocrine therapy, as well as chemotherapy, are eligible.

### Trial registration and ethical approval

EudraCT number: 2018-000279-34

All necessary research governance approvals were sought and approved including REC reference: 18/SW/0045/date of favourable opinion 12/04/2018.

### Randomisation and blinding (Fig. 1)

It was decided to proceed with a three-arm trial for two reasons: (a) both Iscador® M and Iscador® P are recommended by Iscador AG (https://www.iscador.com/de/) for treatment of breast cancer with no evidence for either one being superior to the other, and (b) by having a 1:1:1 randomisation regime, the participants involved will get a better chance of receiving mistletoe therapy, and therefore, it may enhance recruitment.

**Fig. 1 Fig1:**
[figure not shown]
Flow chart of MAB protocol

The patient randomisation list and the medication block randomisation lists will be produced by an in-house statistician at Iscador AG. Randomisation of patients will be conducted by the University Hospitals Bristol Pharmacy (UHBP). Allocation of participants to Iscador® M/Iscador® P/control 1:1:1 ratio will be performed by the UHBP. A separate randomisation list will be held by UHBP for individual emergency unblinding. In the case of a serious adverse event and unblinding being required, the pharmacist will be asked by the principal investigator to look at the unblinding randomisation list using the package coding of the prescription without resulting in the unblinding of all the other patients due to the block randomisation. Both participants and healthcare professionals will be blinded to the group assignment. Any unblinding will be logged by the pharmacy. Breaking the blinding (for a single patient) will only be considered when knowledge of the treatment assignment is deemed essential by the investigator for the patient’s care.

### Intervention group

Participants will receive mistletoe preparations Iscador® M (Maleus) or Iscador® P (Pinus), and these will be available as 1 ml ampoules for subcutaneous injection. The quantity of fermented, aqueous extract from *Viscum album* L. from apple and pine tree respectively used to produce one ampoule of Iscador® product is expressed in milligrams (mgs), e.g. for one ampoule (1.0 ml of solution) of Iscador® M, 1 mg contains the extract of 1 mg fermented apple tree mistletoe. The proposed dose escalating regime is outlined in Table 1. This standard therapy regime was devised from the manufacturer’s recommendation in conjunction with the MAB advisory group. A participant’s therapy is increased from the lowest dose to their optimal dose. The optimal dose for a participant is a dose at which they experience a sustained local skin reaction, still present 24 h after the injection. Such a reaction determines this dose as the dose they remain on for the rest of their trial treatment unless they develop sustained skin reaction of > 5 cm. In cases of skin reactions of > 5 cm, the participants reduce their dose as indicated in Table 1, and this becomes their optimal dose. If a participant does not have a reaction at the maximum dose of 20 mg/ml, that becomes their optimal dose.

**Table 1 Tab1:** Example of typical study therapy and maintenance regime for both Iscador® M (Maleus) and Iscador® P (Pinus)

Induction phase	
**Week 1**	0.01 mg (1.0 ml) × 3 = total of 0.03 mg Iscador M or P
**Week 2**	0.1 mg (1.0 ml) × 3 = total of 0.3 mg of Iscador M or P
**Week 3**	1 mg (1.0 ml) × 3 = total of 3 mg of Iscador M or P
**Week 4**	10 mg (1.0 ml) × 3 = total of 30 mg of Iscador M or P
**Week 5**	20 mg (1.0 ml) × 3 = total of 60 mg of Iscador M or P

### Placebo (control group)

The 1 ml placebo ampoules will have identical external packaging and labelling as the mistletoe ampoules. The placebo is physiological saline 0.90% w/v of sodium chloride, 308 mOsm/L or 9.0 g per litre. Physiological saline has been prepared by the manufacturer of the study medication according to good manufacturing process criteria [5].

### Treatment regime

The study medication will be increased from the lowest dose by the research nurse using the standardised regime until an optimal dose is achieved, and then the participant will stay on this dose for the rest of the study (Table 1). An identical procedure will be carried out with both the Iscador and the saline products. However if the participant is randomised to saline, the same dose will be administered throughout (physiological saline 0.90% w/v of sodium chloride, (1.0 ml)). There is unlikely to be a sustained local reaction with the saline placebo, but essentially, the same rule applies as for the mistletoe arm: the participant would continue on the same saline preparation in week five.

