### Procedures

Participation in the study will be approximately 10 months. Patient informed consent will be taken in BHOC either by the consultant or delegated by the consultant to an appropriately trained and qualified member of the research team. The patients will be given at least 24 h to consider whether they want to participate or not. If a patient decides to take part, they will be randomised into either one of the two mistletoe therapies or a placebo therapy. The first study therapy will be given within a week of randomisation to the study and, ideally, prior to the start of chemotherapy.

The participants treatment regime will be three subcutaneous injections per week. It is advised that the injections will be given every other day, followed by a 2-day break. There will be no breaks in the study therapy regime unless the participants request one, or a clinician advises one. In the case of a participant stopping their standard treatment, they will be encouraged to continue their MAB therapy during this period, but the dose will not be escalated.

Injections will be initiated by research nurses in the clinic with the aim of teaching the participant to self-administer or a nominated person (e.g. relative) to administer to the participant and continue the study therapy at home. The injections will be administered in the abdomen or thigh.

The participants will be given a booklet which contains information on self-administration of the study treatments, the expected responses and potential undesired responses and contraindications of the study therapy and a diary to record their study therapy and responses. The strength of reaction at 24 h after the injection is the indicator for either increasing or maintaining the dose. We estimate that most participants will be able to self-administer their optimal dose within 1 month (~12 visits), and some of these visits will coincide with other treatment or appointments.

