### Sample size calculation and power

Studies suggest there is no formal way of determining numbers for a feasibility trial [12, 13]. The aim of recruiting 45 patients (15 per group) was based on both statistical and practical reasoning. The guidance by Julious is acknowledged which states that for such pilot studies, the recommendation is a sample size of 12 per group [14]. The justifications for this sample size are based on rationale about feasibility, precision about the mean and variance, and regulatory considerations. This decision was discussed with the MAB study team, its steering and advisory groups and the BHOC clinical staff. Overall, this number was chosen to allow fair assessment of the aims of recruitment, retention and completion of outcomes and an assessment of the viability of blinding allowing for some dropouts/withdrawals.

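### Titrating to a skin reaction against plain saline is a likely source of unblinding: the flat blinding statement needs qualifying, and the allocation guess should be reported by reaction

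*Protocol article*

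**What the plan says.** Under Randomisation and blinding the article states: "Both participants and healthcare professionals will be blinded to the group assignment". Under Placebo (control group) the matching described is external: "The 1 ml placebo ampoules will have identical external packaging and labelling as the mistletoe ampoules".

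The dose depends on something that can be seen. Under Intervention group: "The optimal dose for a participant is a dose at which they experience a sustained local skin reaction, still present 24 h after the injection". A reaction over 5 cm leads to a reduction, and a participant with no reaction at the top step stays there. Under Procedures: "The strength of reaction at 24 h after the injection is the indicator for either increasing or maintaining the dose". Under Treatment regime the research nurse does the escalating, and the article concedes: "There is unlikely to be a sustained local reaction with the saline placebo, but essentially, the same rule applies as for the mistletoe arm". Participants also receive a booklet covering "the expected responses and potential undesired responses and contraindications of the study therapy and a diary to record their study therapy and responses".

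Blinding is part of the primary feasibility aim (Design), and the sample size was chosen partly to assess it (Sample size calculation and power). Table 2 assesses the blinding of patients. It records whether they thought they had mistletoe or placebo or did not know, with reasons, and adds interviews and possibly diaries. The Analysis plan asks for the guess in the final questionnaire at T2 and analyses it with Bang's index.

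**The concern.** The sign that drives the dose step is also the sign that separates mistletoe from saline, and both parties described as blinded see it. Matching ampoules on the outside does not hide it. A participant held below the top step, or reduced for a large reaction, has good grounds to think they are on mistletoe, and so has the nurse.

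The pilot is meant to tell the next trial whether blinding is viable, and that trial is to have quality of life, which is self-reported, as its primary outcome. Bang's index by arm averages over reactors and non-reactors. If guesses follow the reaction, the two groups err in opposite directions and can cancel, so that a strong cue looks like random guessing.

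**Working it through.** The plan states no figure on this point, so there is none to reproduce. The check asks how much a reaction reveals, and what the planned index would show.

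**Inputs**
- Allocation: "Allocation of participants to Iscador® M/Iscador® P/control 1:1:1 ratio will be performed by the UHBP" (Randomisation and blinding).
- Size: "The aim of recruiting 45 patients (15 per group) was based on both statistical and practical reasoning" (Sample size calculation and power). So 30 mistletoe and 15 saline are planned, and the prior probability of mistletoe is 30/45 = 67%.
- r, the share of mistletoe participants with a sustained reaction: not given; assumed 40–95%.
- s, the share of saline participants with one: not given, described only as unlikely; assumed 5%, with 20% as a cautious upper case.

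**Step 1: what a reaction reveals.** P(mistletoe | reaction) = 30r / (30r + 15s).

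With s = 5%, 15s = 0.75:
- r = 0.4: 12/12.75 = 94%
- r = 0.6: 18/18.75 = 96%
- r = 0.8: 24/24.75 = 97%

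With s = 20%, 15s = 3:
- r = 0.5: 15/18 = 83%
- r = 0.7: 21/24 = 88%
- r = 0.95: 28.5/31.5 = 90%

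**Step 2: what no reaction reveals.** P(saline | no reaction) = 15(1−s) / [15(1−s) + 30(1−r)], against a prior of 33%. With s = 5%, 15(1−s) = 14.25:
- r = 0.4: 14.25/(14.25 + 18) = 44%
- r = 0.6: 14.25/(14.25 + 12) = 54%
- r = 0.8: 14.25/(14.25 + 6) = 70%
- r = 0.95: 14.25/(14.25 + 1.5) = 90%

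Absence of a reaction is a weak cue unless nearly everyone on mistletoe reacts. At r = 0.8, about 6 of 30 mistletoe participants share the path of about 14 of 15 on saline.

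**Step 3: what Bang's index would show.** The index in an arm is the proportion guessing correctly minus the proportion guessing wrongly. Suppose every reactor guesses mistletoe, every non-reactor guesses placebo, and nobody answers that they do not know. On mistletoe the index is r − (1 − r) = 2r − 1:
- r = 0.4: −0.2
- r = 0.5: 0
- r = 0.6: +0.2
- r = 0.8: +0.6

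At r = 0.5, the 15 reactors are all right and the 15 non-reactors all wrong: (15 − 15)/30 = 0. Within strata the index is +1 and −1. The arm figure reads as random guessing although every guess came from the cue; the split shows it at once. On saline the same rule gives 1 − 2s, that is +0.90 at s = 5% and +0.60 at s = 20%.

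**Step 4: precision.** The 95% half-width is 1.96 × √(4p(1−p)/n), with p the proportion correct. At p = 0.5 (index 0) it is 1.96/√15 = ±0.51 for one arm and 1.96/√30 = ±0.36 for both mistletoe arms pooled. Expected saline reactors are 0.75 at s = 5% and 3 at s = 20%. Stratified results can only be descriptive.

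**The case against.** The pilot sets out to test blinding rather than take it for granted, and it discloses the weakness of saline openly. It collects reasons with each guess, returns to the question in Interview 2, and has diaries that record responses three times a week. A participant who writes that they had a skin reaction has named the cue. Cross-tabulating the guess is also detail that a full protocol or SAP, not shown here, may contain. All of this stands, so the absence of that table from the article is not itself an error. Two things remain: the blinding statement is made without qualification beside text that undercuts it, and the named summary, the arm-level index, can mislead.

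Several stronger readings are tempting, and the documents do not support them.
- **Saline cannot react.** The text says only that a sustained reaction is unlikely.
- **The titration path reveals every allocation.** Mistletoe non-reactors finish on the same path as saline, and a reaction does not tell Iscador M from Iscador P.
- **The pilot cannot attribute unblinding to a cause.** Reasons are collected, though as recollections at T2, well after titration.
- **The saline index will be about +0.90 whatever the mistletoe reaction rate.** That needs every non-reactor to guess placebo. At r = 0.4 and s = 5% a non-reactor is on mistletoe with probability 18/32.25 = 56%, so the better guess is mistletoe. If everyone then guessed mistletoe, the saline index would be −1.
- **Adverse-event attribution, interviews or the booklet are biased.** The article does not say who attributes events or interviews, and the booklet's wording is not shown.
- **Saline should be ruled out for the next trial if reaction predicts allocation.** That condition is expected to be met in advance and has no threshold. What matters is whether guesses follow the reaction.

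**Conclusion.** The point holds in a limited form. By the protocol's own account, reaction-guided titration against plain saline is a likely source of unblinding for participants who react and for the nurse who titrates. The statement under Randomisation and blinding is stronger than the design supports.

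The size rests on assumed reaction rates and the planned 45 participants. A reaction points to mistletoe with probability 94–97% if 5% react on saline and 40–80% on mistletoe, and 83–90% if 20% react on saline and 50–95% on mistletoe. No reaction is much less informative over most of the range. An index of 0 on mistletoe is one possible outcome (half react, all guess from the reaction), not a prediction. How many participants are affected cannot be known until the reactions are tabulated.

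**What to change.** 1. In the blinding row of Table 2 and in the Analysis plan, use diary and clinical report form data to tabulate by arm: sustained reaction (yes/no), any reduction for a reaction over 5 cm, and final dose step (nominal on saline). Report the T2 guess, keeping those who did not know as their own category, and Bang's index by arm within reaction and no-reaction strata, beside the stated reasons. Interpret this descriptively, because cells will be small.
2. Qualify the statement under Randomisation and blinding: allocation is concealed by packaging and labelling, but participants and nurses who see the reaction and dose step may be unblinded. Report them so.

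No dose rule is touched. Both changes remain possible although recruitment has closed (Trial status), provided that the diaries and forms hold the reaction and step. The cost is two descriptive tables with small cells and a slightly less favourable description of the blind.

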### Outcome measures

Feasibility will be measured using mixed methods to assess the following outcomes: recruitment, adherence, acceptability, adverse events, completion of patient outcomes, attrition, blinding and therapy-related symptoms. These are detailed in Table 2 along with the mode of measurement, type of data, measurement of success and analysis plan.

**Table 2 Tab2:** Assessment of the primary aim of the feasibility of the MAB study

Feasibility outcome	Mode of measurement	Quantitative/qualitative	Measurement of success	Analysis
**Recruitment rate**	Clinical report form	Quantitative	Meeting our recruitment target of 45 participants	Narrative numerical reporting
**Specific obstacles to recruitment**	a) Recruitment log b) Qualitative interviews with health professionals	Quantitative and qualitative	a) Complete record of recruitment with reasons for not meeting inclusion criteria or individuals’ reasons for refusal b) Identification of the obstacles to recruitment from health professionals	a) Narrative numerical reporting of recruitment with reasons b) Narrative description of the overarching obstacles identified by health professionals
**Adherence to the study therapy schedule**	a) Clinical report form b) Participants’ diaries	Quantitative	a) Completion of clinical report form b) Completion of diaries and completion of sections with diaries	a) Narrative numerical reporting of completed CRF as participants progressed through trial b) Percentage completion of diaries and completion of items within individual diary sheets (3 per week)
**Acceptability of regular subcutaneous injections**	a) Patient diaries b) Qualitative study	Qualitative	Identification of factors associated with acceptability or not of injection regimes	a) Narrative thematic and numerical report of acceptability b) Formal qualitative analysis from participants and health professional qualitative interviews
**Adverse events from mistletoe and placebo subcutaneous injections**	a) Clinical report form b) (Serious) adverse events report forms	Quantitative	No serious adverse events reported No unexpected or unusual adverse events with mistletoe therapy	a) Narrative numerical reporting b) Numerical and descriptive categories of adverse events and serious adverse events
**Completion of outcome measures**	Participants’ questionnaires	Quantitative	Completion of patient questionnaire and completion of questions within questionnaire	Narrative numerical reporting (%) completion of questionnaires plus % of questions completed within them
**Attrition rate with reasons if possible**	Clinical report form/withdrawal form	Quantitative and qualitative	Reporting of withdrawals and dropouts with reasons	Narrative numerical reporting of withdrawals/dropouts with reasons
**Assessment of blinding of patients**	a) Questions in final questionnaire b) Qualitative interviews and possibly diaries	Quantitative and qualitative	Definitive opinion of the participants with reasons	a) Narrative numerical reporting by participants of whether they thought they were receiving mistletoe/placebo or did not know plus reasons b) Narrative reporting of additional reasons for identifying allocation of treatment
**Assessment of therapy-related symptoms and health-related quality of life in the sample population**	a) Participants’ diaries b) Qualitative interviews	Qualitative	Identification of therapy-related symptoms and general quality-of-life descriptions	a) Narrative thematic and numerical report of symptoms and descriptions of quality of life b) Formal qualitative analysis from participants

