### Participant diaries and questionnaires

Participants will receive a diary card pack to record their study therapy and responses three times a week to correspond with the MAB study regime.

The MAB questionnaire pack comprises six questionnaires and will be administered at three time points during the trial: *time point 0 or baseline* — following randomisation and before the start of chemotherapy regime; *time point one* — following the 3rd cycle of chemotherapy; and *time point two —* 4 weeks after the last standard treatment (chemotherapy with or without radiotherapy), on the day of the last study treatment. The questionnaires included are as follows:European Organization for Research and Treatment of Cancer (EORTC) QLQ-C30 (quality of life — cancer 30 items) questionnaireEORTC QLQ-BR23 (quality of life — breast cancer 23 items) questionnaire [6, 7]Functional Assessment of Cancer Therapy-Neutropenia (FACT-N) scale [8]Cancer fatigue scale [9]Autonomic regulation scale [10]The CompleMentary and Alternative Beliefs Inventory (CAMBI) [11]

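### Therapy adherence is defined only by how completely forms and diaries are filled in, which is at best a loose proxy for injections taken

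*Protocol article*

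**What the plan says.** The protocol article, under Outcome measures, includes adherence among the feasibility outcomes and refers the reader to Table 2 for how each is measured, judged and analysed. The therapy-adherence row is classed as quantitative. Its cells read as follows.

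- Data sources: "a) Clinical report form b) Participants’ diaries".
- Measurement of success: "a) Completion of clinical report form b) Completion of diaries and completion of sections with diaries".
- Analysis, part a: "Narrative numerical reporting of completed CRF as participants progressed through trial".
- Analysis, part b: "Percentage completion of diaries and completion of items within individual diary sheets (3 per week").

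Two other sections bear on what could be measured. Participant diaries and questionnaires states: "Participants will receive a diary card pack to record their study therapy and responses three times a week to correspond with the MAB study regime". Procedures states: "The participants treatment regime will be three subcutaneous injections per week". Procedures also allows breaks in study therapy at the participant's request or on a clinician's advice.

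The Analysis plan section adds no dose-based measure. Its one use of the word adherence concerns which questionnaires to carry into the full trial.

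**The concern.** The row names one quantity and measures another. Adherence to an injection schedule is a statement about doses, whereas the row counts completed records. Table 2 has a separate row for completion of the outcome questionnaires, and its success measure is framed in the same way: forms completed, and items completed within them. That framing suits a data-completeness outcome. Applied to therapy adherence, it produces a second completeness outcome and leaves dosing without a stated count.

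This matters because feasibility is the trial's primary aim. After training, participants or a nominated person inject at home, three times a week, during chemotherapy. A full trial would need to know what fraction of the scheduled injections was taken. A participant who stays in the study but skips doses is not a withdrawal, and if that participant keeps up the diary, no quantitative outcome as stated would show the skipped doses.

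The article fixes both the success measure and the analysis for this row, so the point is not a detail left for an analysis plan or the full protocol to supply.

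**Working it through.** The documents give no adherence figure to reproduce. The check is a reading of the row followed by a short illustration.

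**Step 1: what is counted.** Of the five descriptive cells in the row (outcome name, source, type, success, analysis), only the name refers to the therapy schedule. The success and analysis cells refer to completion of CRFs, diaries and diary items. Doses taken, missed or due do not appear.

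**Step 2: what is available.** The diary is meant to record study therapy three times a week, which supplies the numerator. The schedule is three injections a week, which supplies the denominator. Both come from the protocol article (Participant diaries and questionnaires; Procedures).

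**Step 3: size of the denominator.** Procedures gives participation as about 10 months.

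- Weeks = 10 × 52/12 = 43.3.
- Injections due = 3 × 43.3 = 130.

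This assumes dosing throughout the 10 months with no breaks, so it is an illustrative upper bound. At 8 months the figure is 3 × 8 × 52/12 = 104, and at 6 months 3 × 6 × 52/12 = 78.

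**Step 4: the two measures compared.** Let the record measure be sheets completed ÷ sheets due, and the dose measure be injections taken ÷ injections due. The three participants below are assumed, with 130 injections and 130 sheets due.

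| Participant | Injections taken | Sheets completed | Record measure | Dose measure |
|---|---|---|---|---|
| A: half the doses, every sheet | 65 | 130 | 100% | 50% |
| B: every dose, half the sheets | 130 | 65 | 50% | 100% |
| C: both at 80% | 104 | 104 | 80% | 80% |

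The percentages do not depend on the figure of 130. Participant A is overstated by 50 points, participant B is understated by 50 points, and C shows no error. The measures agree only when recording follows dosing.

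**Step 5: would the repair tell them apart?** Suppose the completed sheets are accurate, and compute injections recorded as taken over injections due in two ways.

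- A, missing sheets as not taken: 65/130 = 50%. Missing sheets excluded: 65/130 = 50%, since none are missing.
- B, missing sheets as not taken: 65/130 = 50%. Missing sheets excluded: 65/65 = 100%.

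A's two figures agree at the true value. B's differ, and the gap shows how much of the result rests on missing records. Reported with the completion percentage (100% for A, 50% for B), the pair separates the two cases.

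**The case against.** The strongest reply is that the diary is tied to the injections. Three sheets a week are due and three injections a week are due, so each scheduled dose has one sheet. If participants complete a sheet only when they inject, sheets completed over sheets due is already doses recorded over doses due, with missing sheets counted as not taken. Participant A then could not occur. The diary card and the CRF are not shown, so this cannot be ruled out. That much stands, and it is why completion should be called a loose proxy. A reader might infer that the adherence result would measure paperwork and nothing else. The documents do not support that. Equally, they do not say that a missed dose leaves a blank sheet, so the proxy cannot be relied on. The error in the other direction, injecting without completing the sheet, remains under either reading.

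A reader might also infer that the trial could say nothing about whether three injections a week can be sustained. That goes too far as well. Table 2 provides for withdrawals with reasons and for a thematic and numerical report on the acceptability of the injections. The Analysis plan reports retention by arm at T1 and T2, and the interviews cover administration of the therapy. These address the question in part. None of them is stated as a count of doses.

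Finally, it may be said that the investigators would tabulate the therapy entries anyway, or that the full protocol provides for it. The article does not say those entries will be ignored. But it sets out a specific measure and analysis for this outcome, and nothing in it commits anyone to a dose count.

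**Conclusion.** The concern holds in a limited form. As written, the adherence outcome is completion of records, which is a loose proxy for injections taken and cannot separate missed dosing from missed recording. The error can run in either direction, and its size depends on how often recording and dosing diverge, which the documents do not allow anyone to estimate. The 50-point differences above come from assumed participants and are not predictions.

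The consequences are bounded. The row has no success threshold, no progression rule depends on it, the analysis is descriptive, and no figure in the document is wrong. The fault lies in the stated measure, not in data collection. It is still worth correcting, because this is a named outcome under the primary aim and no other stated quantitative outcome counts doses.

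The conclusion assumes that the diary or CRF entry shows whether each scheduled injection was taken, which is how the article describes the diary's purpose.

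**What to change.** Redefine the success and analysis cells of the therapy-adherence row as follows.

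1. For each participant, adherence is injections recorded as taken divided by injections due. Injections due are 3 per week from the first injection to T2 or withdrawal. Summarise by arm.
2. Identify breaks requested by the participant or advised by a clinician, so that they are visible apart from unexplained missed doses.
3. Give the result twice: once with missing sheets counted as not taken, and once with them excluded. The first figure alone would keep the understatement already present in the completion measure.
4. Report diary and CRF completion separately, labelled as data completeness.

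Splitting the result by period, for example before and after T1, is optional; with 15 participants planned per arm it would be descriptive only.

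The cost is revised wording and a little more analysis. The diaries and CRF are already the row's data sources, so no new data, visits or participants are needed.
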